### Qualitative analysis

We will explore the experiences of patients and stakeholders while using the CFL-TB tool through focus group discussions and key informant interviews. We will use purposive sampling and continue data collection until saturation is achieved [52]. Participants will be stratified by gender, age, and use of the tool. We will use the thematic analysis approach to determine what participants and other stakeholders experience and perceive. The conventional content analysis approach will be used; the coding categories will be derived directly from the text data [53]. Preliminary data analysis will occur concurrently with the data collection. The process of proofreading transcripts and notes will help draw attention to emerging and a priori themes. Themes then form a framework for a codebook. During the coding process, the codebook will be adapted and quotations that are illustrative of participants’ perspectives and experiences regarding the issues being studied will be identified and used in the presentation of the findings. Using the directed qualitative analysis approach [53], we will explore the relationships between the intervention and treatment outcomes using the IMB model [36] as a guide theory.

### Sensitivity analysis

To determine the impact of nonadherence to the study intervention, we will stratify the analysis by utilization of the CFL-TB tool. For both primary and secondary quantitative endpoints, we will conduct an overall and stratified analysis by HIV status, TB type (pulmonary versus other forms of TB), and gender.

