### Trial endpoints

The primary endpoint is treatment success (at 6 months): treatment success is a composite outcome, comprising treatment completion and cure in patients with clinically and bacteriologically diagnosed TB, respectively. It is a robust and agreed indicator of treatment success in TB programs. In patients with bacteriologically diagnosed TB, cure is defined as having a negative sputum test in the last month of treatment and on at least one previous occasion [47]. For clinically diagnosed patients, completion entails 6 months of therapy. The denominator for each arm will be the number of patients enrolled. At the same time, the numerator is the sum of bacteriologically and clinically diagnosed patients with cure or treatment completion, respectively.

This RCT also has several secondary endpoints. First, we will determine the TB cure rates in patients with microbiologically diagnosed TB. Second, we will determine treatment completion for patients clinically diagnosed with TB in the two arms: Third, retention rates will be determined and compared between the study arms. Patients will be deemed to be actively engaged in care if they attend a clinic visit within one month of a scheduled appointment. Additionally, we will compare appointments. We will categorize visits as “early,” if they present before an appointment, “prompt” if they show up within three days after the appointment date, “late” if they present after three days but within 30 days of a scheduled appointment and missed if patients do not show up at all or present after 30 days. Fourth, we will determine the incremental costs per additional DALY averted per percentage point increase in treatment success in the intervention versus the control arm. In addition, we will compare adherence rates at months 2 and 6. Depending on the availability of drug susceptibility tests, we will compare the rates of MDR-TB. To understand the impact of the intervention on the treatment outcomes and the potential for adoption and scaling of the intervention, we will explore the perceptions and experiences of patients and care providers towards the MHI. Finally, we will determine the uptake and adherence to the intervention. We will consider the successful receipt of a reminder as a proxy for the utilization of the technology. Therefore, we will determine the proportion of successful calls in the intervention and control arms.

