### Sample size determination

Based on results from a randomized controlled trial in Kenya that demonstrated a 9% increase in TB treatment success following the use of SMS [12], we hypothesize that the interactive voice response platform will lead to at least a 6% higher impact as compared to SMS reminder treatment success (i.e., a 15%-point difference compared to the control arm). A retrospective cross-sectional study of routine data on HIV/TB co-infected patients from the Uganda National Tuberculosis and Leprosy Program reported lost to follow-up rates of 3.5% and 16.6% in urban and rural settings, respectively [7]. The rate of lost-to-follow at the three TB clinics was approximately 11.8%. Therefore, assuming an 11.8% lost-to-follow-up rate, this study would require a minimum of 274 (137 patients per arm) patients to demonstrate a 15% increment in treatment success with a power of 0.8 and precision of 0.05.

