### Analysis of endpoints

The planned analyses are summarized in Table 2. We will use a two-tailed *p* value of 0.05 and report the 95% confidence intervals for all endpoints. In all analyses, we will control for confounders of adherence and retention [7, 48, 49]. In both primary and secondary outcomes, we will undertake per-protocol and intention-to-treat analyses.

**Table 2 Tab2:** Analysis of quantitative outcomes

Outcomes	Measure of outcomes (intervention versus control arm)	Statistical analysis
Treatment success	Proportion of patients with treatment success at six months. Odds ratio of treatment success	Logistic regression, odds ratios
Cure rates	Proportion of patients cured of TB; odds ratio of TB cure	Logistic regression, odds ratios
Treatment completion	Treatment completion rate; odds ratio of treatment completion	Logistic regression, odds ratios
Retention in care	Hazards of attrition in the intervention versus control; Cumulative attrition at six months	Cox’s proportional hazards model, log-rank test
Adherence to TB medicines	Mean adherence rates (proportion of TB medicines)	Mann-Whitney U test and Poisson regression
Appointment keeping and punctuality	Proportion of patients who keep an appointment; Proportion of patients with early, prompt, and late visits	Ordered logistic regression
Drug-resistant TB rates	Proportion of patients with rifampicin-resistant TB	Logistic regression, odds ratios
Call success rates (2,4, and 6 months)	Proportion of successful calls	*t* test

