### Analysis of the primary endpoint

We will use logistic regression to determine the crude and adjusted odds ratios of treatment success in the intervention arm versus the control arm. The multivariable model will adjust just for potential confounders, including age, sex, employment status, bacterial load at baseline, TB category, and HIV status [7, 48, 49]. The stepwise backward elimination method will be used to fit the final model. The model with the lowest Akaike information criterion (AIC) statistic will be considered the best fitting. Covariates with a global/trend *p* value > 0.2 at the bivariate analysis, will be adjusted for in the final multivariate model. We will explore factor interactions, including the interaction between age adherence and sputum smear results at baseline. Where interaction is confirmed, we report both the main and interaction effects.

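### Subgroup effects by HIV status, TB type and gender are to be examined by stratified arm comparisons, and no arm-by-subgroup interaction test is named, so the stated plan does not test whether the effect differs between subgroups

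*Protocol article*

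**What the plan says.** The Sensitivity analysis section of the protocol article states its scope as "For both primary and secondary quantitative endpoints" and its method as "we will conduct an overall and stratified analysis by HIV status, TB type (pulmonary versus other forms of TB), and gender". Three two-level factors give six strata per endpoint.

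The Analysis of endpoints section sets one threshold: "We will use a two-tailed *p* value of 0.05 and report the 95% confidence intervals for all endpoints". It adds "In both primary and secondary outcomes, we will undertake per-protocol and intention-to-treat analyses".

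Interactions appear only under Analysis of the primary endpoint: "We will explore factor interactions, including the interaction between age adherence and sputum smear results at baseline", followed by "Where interaction is confirmed, we report both the main and interaction effects". Study arm is not mentioned as one of the interacting factors, and neither are HIV status, TB type and gender.

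The trial has a single primary endpoint: "The primary endpoint is treatment success (at 6 months): treatment success is a composite outcome, comprising treatment completion and cure". The sample size is set on that endpoint alone: "a minimum of 274 (137 patients per arm) patients to demonstrate a 15% increment in treatment success with a power of 0.8".

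**The concern.** Whether an intervention works differently in two groups is a question about the difference between two effects. A separate comparison in each group does not answer it. Two strata with the same true effect will often fall on opposite sides of 0.05 because they differ in size or by chance. The article uses stratification for the three factors where a subgroup question arises, and names an interaction only for other variables.

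This matters because the article aims to inform national TB policy and expects scale-up if clinical effectiveness is shown. A table with p<0.05 in men but not in women, or in pulmonary but not other TB, could be read as a reason to target the intervention when the data show no such difference.

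**Working it through.** **1. The plan's own figure.** The article gives the difference (15 points), power (0.8), two-sided 0.05 and loss (11.8%), but no control success rate. Assuming 70% v 85%, the pooled two-proportion formula gives 121 per arm. Then 121/(1 − 0.118) = 137.2, rounded up to 138, or 276 in total against the stated 274. An assumed 71% v 86% gives 266. So 70% v 85% is consistent with the plan and is used below.

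**2. Strata sizes.** The article gives no shares. I assume 40/60 for HIV status, 85/15 for TB type and 60/40 for gender. Of 121 evaluable per arm, this gives 48.4 and 72.6 (HIV status; the same two sizes for gender), and 102.8 and 18.2 (TB type).

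**3. Power within a stratum of n per arm, same true effect everywhere.**

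Power = Φ{[0.15 − 1.96·√(2·0.775·0.225/n)] / √[(0.7·0.3 + 0.85·0.15)/n]}

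- n = 48.4: (0.15 − 0.1664)/0.0835 = −0.20, power 0.42
- n = 72.6: (0.15 − 0.1358)/0.0682 = 0.21, power 0.58
- n = 102.8: power 0.73
- n = 18.2: power 0.19

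**4. Chance that exactly one of the two strata is significant,** P = a(1 − b) + b(1 − a):

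- HIV status or gender: 0.422·0.418 + 0.582·0.578 = 0.51
- TB type: 0.734·0.814 + 0.186·0.266 = 0.65

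Treatment success is defined over everyone enrolled. With 137 per arm instead of 121, the same formula gives 0.51 and 0.67, so the result does not depend on that choice.

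**5. No effect at all, primary endpoint only.** Simulating 274 patients allocated 1:1, with the three factors overlapping in the same patients, at least one of the six strata gives p<0.05 in either direction in about 21% of trials.

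**6. No effect on any endpoint, all comparisons.** Leaving out call success, Table 2 has seven between-arm outcomes. Overall plus six strata gives 7 × 7 = 49 tests. Simulated probability of at least one p<0.05, by assumed correlation between endpoints:

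| Correlation | Either direction | Favouring CFL-TB |
|---|---|---|
| 0 | 0.82 | 0.55 |
| 0.3 | 0.77 | 0.46 |
| 0.5 | 0.69 | 0.38 |
| 0.8 | 0.52 | 0.28 |

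Running both per-protocol and intention-to-treat analyses was not modelled and would raise these somewhat.

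**The case against.** The strongest reply has four parts.

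- **The article does not spell out stratum p values.** The 0.05 rule is written for endpoints, and strata are not endpoints. The stratified analysis could be no more than estimates with intervals. This stands in part: the article does not say that significance will be compared across strata. But nothing limits the strata to description, and no other method is given for these three factors.
- **The interaction list is open-ended.** This stands: arm-by-HIV, arm-by-TB-type and arm-by-gender are not excluded. They are also not named, while a different interaction is.
- **Detail may sit in the analysis plan or full protocol, which are not shown.** This disposes of any complaint that the article lacks a hierarchy or multiplicity adjustment for secondary endpoints. One primary endpoint is named, the trial is sized on it and the rest are called secondary. It does not dispose of the choice of method that the article does state.
- **The 49-test model is rough.** This stands. Cure and completion apply to different patients and together make up the primary endpoint, drug-resistance testing is conditional on availability, and shares and correlations are assumed. The results in steps 3 to 5 of the working do not use this model.

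A reader might also infer that a false claim of benefit somewhere is more likely than not. The figures do not support that. Only about half of two-sided errors favour the intervention, and the probability of a false benefit is below one half at every correlation examined from 0.3 up. Nor does the article contain any rule by which a secondary endpoint or a stratum could carry a claim of benefit.

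**Conclusion.** The point holds as one about method. For HIV status, TB type and gender the article states stratified comparison and names no test of whether the effect differs. If the strata were read by significance, a perfectly uniform 15-point effect would look like a subgroup difference in about 51% of trials for HIV status or gender and 65% for TB type. With no effect, about 21% of trials would show at least one significant primary-endpoint stratum. Across all 49 comparisons, a false positive in either direction has probability of about 0.5 to 0.8, and a false benefit about 0.3 to 0.55, for correlations from 0.8 down to 0.

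These sizes rest on assumed success rates of 70% v 85%, assumed strata shares and, for the 49 tests only, assumed correlations and no effect on any endpoint. The primary comparison itself is unaffected. The change is worth making because it is cheap, but it does not threaten the trial's main conclusion.

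**What to change.** In the Sensitivity analysis section, state that each of HIV status, TB type and gender will be assessed by one arm-by-subgroup interaction test in the primary logistic model. State that stratum estimates will be shown with 95% confidence intervals as descriptive, without stratum p values, for the primary and secondary quantitative endpoints. No change to the status or ordering of the secondary endpoints is asked for.

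The cost is wording and three model terms, with no new patients or data. There are two limits to accept:

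- **Low power.** The variance of a stratum log odds ratio is 1/(0.21n) + 1/(0.1275n). For n = 48.4 and 72.6 this is 0.260 + 0.174 = 0.434, a standard error of 0.66 for the interaction. The observed odds ratios would have to differ by a factor of about exp(1.96 × 0.66) = 3.6 to reach 0.05. A non-significant interaction is therefore not evidence that the effects are equal.
- **Some false positives remain.** Three interaction tests at 0.05 give at most 3 × 0.05 = 0.15 chance of one false signal, so a positive interaction should be treated as a lead. A stratum result can no longer support a claim on its own.

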### Interim analysis

There will be no preliminary analysis, as this study does not pose a significant risk to participants.

### Ethical considerations

The study protocol was approved by the Makerere University School of Medicine Research Ethics Committee (SOMREC) (Approval #:2019-149) and the Uganda National Council of Science and Technology (UNCST) ((Approval #: HS524ES). Any protocol amendments will be reviewed and approved by SOMREC and UNCST. Therefore, we will follow the UNCST guidelines [45, 54], the Declaration of Helsinki [55], and good clinical practice [56] during the study implementation. Before participation, the study staff will screen and obtain written informed consent from all prospective participants and their care providers. There will be no additional requirement for consent before obtaining biological specimens, including blood samples and sputum, as these are part of the standard of care.

### Protocol amendments

The initial protocol (version 1.3, approval date November 07, 2019) (Supplementary File 1) was amended, and protocol version 2.0 was approved by SOMREC and UNCST on March 22, 2021. The major changes included a provision for phone-based reviews and an additional two study sites. Supplementary File 2 provides details of the changes made in protocol version 2.0. The latest approved protocol version 2.0 is provided as Supplementary File 3.

### Confidentiality of participant data

To ensure the safety of the participant data, data are regularly entered into a database hosted on the IDI server. The data on the CFL-TB backend were encrypted. Access to the system database is password-protected and inactivity for more than 30 min on the CFL-TB web interface logs the web user out. The system generates a log of admin logins and the changes to the web interface. Patients calling on CFL-TB are authenticated by their registered mobile number and must key-in their PINs before listening in to the calls. The software does not reveal its own identity to the person called until the person has been authenticated as a registered patient (only CFL-TB signature music is played). The Analysis datasets will be anonymized before data analysis by assigning participants with pseudo identification numbers (IDs) delinked from the study IDs. Phone call records will not be disclosed but may be used for matching data.

### Adverse events reporting

At each visit, participants will be interviewed on any ongoing symptoms and hospitalizations since their prior visit. The CFL-TB platform will maintain a patient toll-free number, and patients will be asked to initiate calls when they want to communicate with HCWs. All adverse events (AEs) will be graded using the Division of AIDS (DAIDS) table for adverse events [57]. Serious adverse events (SAEs) will be reported to IRBs. The investigator will assess the relatedness and causality of AEs to mobile phone use.

### Study oversight and monitoring

The design, implementation, and evaluation of this study will be monitored by an independent scientific advisory board (SAB). The SAB comprises eminent community members, policymakers, scholars, and scientists. There will be no data safety monitoring board, as the study does not pose a significant risk to participants. Any suggested protocol amendments will be reviewed by the SAB before submission to IRBs for approval. The IDI research department will monitor the study progress annually.

### Dissemination plan for research findings

Dissemination of the results of this study will follow the institutional dissemination policy (IDI) and national regulations on data privacy [45]. We aim to publish the results and present data at national, regional, and international conferences. The study has been registered with clinicaltrials.gov (NCT04709159). Since we aim to influence the TB policy in Uganda and other LMICs, we will present the results at local meetings with policymakers. Policy briefs will be presented to the National TB and Leprosy Program of the Ministry of Health. We will also conduct community dissemination meetings and communicate the results of this study to the participants and care providers.

## Discussion

This study is a multicenter, open-label, randomized controlled trial to determine the impact of IVRT-based MHI on TB treatment outcomes. The study will compare treatment success at six months in participants with confirmed drug-susceptible TB randomized to the intervention and control arms. The secondary outcomes include TB cure rates in participants with pulmonary TB, appointment keeping, adherence to treatment, and attrition from care. Participants in the intervention arm will receive adherence and appointment reminders and health tips and will also have options for reporting symptoms remotely. We will also use mixed methods to determine the acceptability of the intervention, its cost-effectiveness, and its impact on TB treatment outcomes.

This study is not without justification. In 2018, there were 10 million cases of TB, with 1.45 million deaths, 250,000 of whom were patients living with HIV/AIDS (PLHIV) [1]. The disease has also harmed other health sectors [58]. However, whether MHIs can significantly contribute to a sustainable TB response is unknown. The growth of the mobile phone industry is highest in countries with weak health systems and a high burden of TB [59]. Mobile phone ownership is also high in patients with TB [19], especially among men, the population most affected by TB [1, 38]. Therefore, the delivery of the intervention at the population level is feasible.

In most LMICs, the *sine qua non* for the success of MHI is the implementation fidelity and tailoring the technology to the local context. Previous studies have demonstrated that technical difficulties are a barrier to the use and scale-up of MHIs. These include power outages and sparse network signals, especially in rural communities [33, 60]. Additionally, only 55% of Uganda is geographically covered by the Internet [24]. Thus, MHIs that have previously been demonstrated to be efficacious, including video technology [25], are not implementable in many LMICs.

To enhance the scale-up of MHIs, the proposed interventions must be interoperable with existing MHIs and technologies. To this end, the Ugandan government requires MHIs to be sustainable, compliant with data privacy, and interoperability with existing MHIs [61]. The IVRT under investigation meets this requirement as it is interoperable with DHIS2, the only national database for health reporting in Uganda. Additionally*,* confidentiality concerns are common among all MHIs. A study involving the use of IVRT to support the adoption of TB preventive therapy in Ethiopia has reported confidentiality, stigma, and trust in HCWs as critical determinants of the acceptability of MHIs [33]. However, concerns about privacy and refusal to participate in MHIs are generally low in Uganda [28, 62]. The Sharing of mobile phones outside households is also rare [63]. However, MHIs have an inherent risk of data privacy breaches that must be mitigated. Therefore, data will be double-encrypted, system upgrades will be version controlled, and participants will use PIN before receiving reminder calls.

Although several frameworks for mobile health application development exist, HCD is increasingly preferred in resource-limited settings [64, 65]. The HCD approach ensures higher usability of interactive systems by integrating human factors such as human knowledge and techniques in the prototype development [66]. This approach has been used to develop other TB health information systems in sub-Saharan Africa [65]. As emphasized by the principles of HCD [64], software development involved a multidisciplinary team and broader stakeholder engagement. Such an approach ensures the uptake and scaling of MHI in LMICs [32].

We envisage the challenges in the implementation of this study. In a pilot project that evaluated the use of IVRT to enhance access to child health care services in Ghana, the critical barriers to the adoption of the IVRT were lack of human interaction, lack of refresher training, and the lack of social integration of the system [35]. Therefore, we will conduct regular refresher training for staff. Similarly, the study staff will interview participants at every study visit and ensure they have no challenges in using the tool. The software is compatible with feature phones which have the greatest penetration in Uganda [67]. On the other hand, the significant reasons for the success of the pilot project were the ability of the technology to support local languages, quality of the service, health education, and empowerment of end-users. Daftary et al. also reported individualizing MHIs as an enabler of acceptability [33]. To this end, we will individualize appointment and adherence reminders by allowing patients to select the preferred reminder frequency and their timing. However, contextualizing intervention is very difficult to achieve in Uganda because of cultural diversity [68] and limited technology options. We used several major local languages spoken in Uganda. Our IVRT allows for two-way communication and therefore allows human interaction. In the implementation phase of the project, we will offer refresher training to patients and staff on how to use the technology.

